**Methods:**

About 21,000 women aged 46–67 years compliant to screening mammography are expected to be enrolled. At enrolment, information on well-known breast cancer risk factors and life-styles habits are collected through self-admistered questionnaires. Information on breast density and anthropometric measurements (height, weight, body composition, and waist circumference) are recorded. In addition, women are requested to provide a blood sample for serum, plasma and buffy-coat storing for subsequent molecular analyses within the nested case-control study. This investigation will be performed on approximately 233 cases (screen-detected) and 699 matched controls to evaluate SNPs and circulating microRNAs. The whole study will last three years and the cohort will be followed up for ten years to observe the onset of new breast cancer cases.

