### Study setting

The eligible population of the study consists of 46–67-year-old women invited to breast screening in the cities of Turin and Biella (two Northern Italian cities in Piedmont), where BC screening is a long-standing practice well known by the people living in the area [4]. For organizational reasons the Andromeda study is conducted simultaneously with another investigation, the Proteus study (NCT02590315), a randomized controlled trial aimed at comparing the performance of digital breast tomosynthesis (DBT) with those of standard digital mammography (DM). The study duration is planned for three years. Enrolment started in July 2015 and by the end of the recruitment phase (December 2017) about 21,000 women are expected to be included in the study. The women cohort will be followed up for additional ten years after the study ending through the screening archives to observe the onset of new BC cases.

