**Fig. 1 Fig1:**
[figure not shown]
The Andromeda Study

Women who agree to participate in Andromeda are asked to fill in a short risk questionnaire (SRQ - Additional file 1) to collect information on general BC risk factors (reproductive and BC family history, previous breast biopsies, basic physical activity level, body mass index and alcohol consumption), immediately at the enrolment desk.

In addition, they are asked to fill in a long risk questionnaire (LRQ - Additional file 2) on diet, physical activity, smoking habits, general state of health and psychological distresses (sections on physical activity and on dietary habits were modified from the EPIC questionnaires [25], the section on psychological distresses was taken from the Brief COPE questionnaire [26]). Women are also invited to undergo anthropometric measurements (height, weight, body composition, and waist circumference) and to provide a blood sample for serum, plasma and buffy-coat storing. Blood specimens are aliquoted, processed and stored at −80 °C. These last procedures can be performed at the time of the examination or at a later date, to be agreed with the woman; fasting is not required.

Mammograms derive either from DM or from DBT (according to the Proteus trial randomization) and are read by two expert radiologists. Breast density is calculated during breast examination, through a specific algorithm [27] and it is classified into categories by means of the Breast Imaging Reporting and Data System (BI-RADS) [28].

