### Statistical power and analysis

All the data collected through the SRQ will be used to obtain the risk estimates based on a risk prediction model that has been developed for the Italian population and validated on an independent cohort of Italian women (Petracci score) [32].

This information, along with the information on breast density, lifestyle related risk, polygenic risk score from miRNAs and SNPs will be modeled in respect of BC risk factors onset.

As they are determined on the same subjects, among women with abnormal mammography, the most efficient estimate of the ratio between relative (positive vs negative) positive predictive values (PPV) ratios, for any couple of the above factors is given by:$$ PPV\; ratios=\frac{cancers\;\left(\kern0em positive to factor1\; but\; not to factor2\right)\kern0.5em \times \kern0.5em non cancers\;\left(\kern0em positive to factor2\; but\; not to factor1\right)}{cancers\;\left(\kern0em positive to factor2\; but\; not to factor1\right)\kern0.5em \times \kern0.5em non cancers\;\left(\kern0em positive to factor1\; but\; not to factor2\right)} $$

Assuming that 40% of 21,000 enrolled women have a dense breast, 20% a certain Petracci score, 50% a lifestyle risk and 20% a given miRNA, that 11‰ of study women carry BC and that the overall PPV of mammography is 20%, some 100–120 discordant cancers and 640–740 discordant women with abnormal mammography but no cancer are expected for the considered couples of factors. Under these assumptions, the study has about 80% power to reject (alpha = 0.05) the null hypothesis that the relative PPV ratio equals 1 if its true value is at least 1.8–2.0, depending on the couple of factors considered.

To calculate the sample size necessary for biomarkers pivotal evaluation (expressed on a continuous scale), minimally acceptable and desirable levels of typical performance measures of interests, such as the true-positive rate (TPR) and the false positive rate (FPR) have been defined. For general population screening, the FPR must be quite low to avoid huge numbers of people undergoing unnecessary costly medical procedures. Thus a maximally acceptable false-positive rate (FPR0) of 4% (the minimally acceptable specificity is therefore 96%) and a minimally acceptable sensitivity of 80% (TPR0) were hypothesized. The null hypothesis to be rejected is the following: H0: TPR0 ≤ 0.80 or FPR0 ≥ 0.04.

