The sample size required with an 80% power (alpha = 5%) and assuming desirable true-positive rate and false-positive rate of TPR1 = 0.90 and FPR1 = 0.05, respectively, was of 179 cases and 537 controls. Sample size computation was based on theory on the Receiver Operating Characteristic (ROC) curve.

Assuming an annual BC detection rate (DR) of 0.006 in the first year and 0.005 in the second year of the study (therefore the biennial DR considered was 0.011) a total of 233 case patients in the first two years of the study are expected to be observed, thus exceeding the 179 required. These estimates are based on DRs observed in the previous years in the same centers considered in this study (Turin, Biella) [4]. Thus, the molecular analyses will be performed on 233 cases and 699 matched controls. For each case, three control subjects will be selected from the cohort of women, on the basis of the following criteria: no history of cancer, similar age at enrolment (within 5 years), similar race, availability of blood sample, similar date of blood draw.

Moreover, circulating miR-18a, miR-181a, and miR-222 levels - derived from the sister study cohort [21] - on plasma collected from all the women enrolled that have at least one first degree relative with BC will be assessed. The estimated number of this subgroup is 1800 women, 40 of which are expected to develop BC within 18 months, and will therefore belong to the case group.

To assess the predictive ability of the considered criteria (i.e., breast density, absolute risk of developing BC and, lifestyles) in identifying groups of women with different risk levels, the positive and negative predictive values and ratios of predictive values (PPV and PPV ratios) will be calculated for each criterion.

The discrimination ability of single biomarkers will be evaluated by means of the ROC curves, whereas to test if biomarker levels are significantly higher or lower in cases and controls, logistic regression models will be used. To evaluate the association between women’s characteristics or tumor features and biomarker level, linear regression models will be adopted.

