Particular attention is given to the formulation and administration of the LRQ, taking care to avoid overlap with the SRQ, reducing compilation times and trying to get standardized and comparable answers. The SRQ has been specifically designed for tablet devices to minimize both time and errors in inputting data.

Another concern is related to the molecular analyses. Since we do not know if specific miRNA levels fluctuate according to age or other demographical parameters or smoking exposure, we plan to use age and smoking matched patients without any diagnosis of (pre)malignant disease as controls for the miRNA analysis on plasma samples.

To face problems related to evaluation of miRNA expression particular caution is adopted especially regarding sample handling, timing and procedure of plasma separation, storage prior to extraction and protocols for RNA extraction and yield control. Our measures should be reliably translated in a screening context, therefore we analyze microRNAs already tested in prospective studies on plasma of cases before diagnosis and on matched controls, and validated using NGS approaches or Taqman on gene cards on independent cohorts.

A strength point of the study is represented by the prospective uniform nature of specimen collection for all subjects from a single cohort. This eliminates systematic biases by ensuring that case patients and control subjects are collected in exactly the same way and, in this case, from the setting for which biomarker is intended, that is the standard screening setting. Moreover, collecting and storing specimens before ascertaining the clinical diagnosis may provide information on the time dimension, that is, if the levels of the biomarker deviate from those in control subjects close to the time of clinical diagnosis, then the biomarker shows little promise for screening. On the other hand, if levels in case subjects reach levels distinct from those in controls years before clinical diagnosis, then the biomarker’s potential for early detection is increased.

Finally, the retrospective component of the design also avoids ethical problems, such as knowing the biomarker value without knowing how it should affect patient care. Moreover, sample storing will allow us future discovery, if more standardized and reliable techniques will become available, of novel circulating molecules whenever those selected will not satisfy our expectance.

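### Cancer history excludes women from the controls but not from the cases, so the FPR describes a cleaner group than the screened population

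*Protocol article*

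**What the plan says.** All references are to the protocol article.

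- **Cohort** (Study setting): "The eligible population of the study consists of 46–67-year-old women invited to breast screening in the cities of Turin and Biella". No cancer-history criterion is stated.
- **Cases** (Abstract, Methods): "This investigation will be performed on approximately 233 cases (screen-detected) and 699 matched controls". Being screen-detected is the only stated requirement.
- **Controls** (Statistical power and analysis): "three control subjects will be selected from the cohort of women, on the basis of the following criteria: no history of cancer", followed by similar age, race and date of blood draw, and an available blood sample.
- **Controls again** (Discussion): "age and smoking matched patients without any diagnosis of (pre)malignant disease as controls". This is stricter, because it adds premalignant disease, and it too concerns controls only. The two control rules also differ on smoking; that is a separate matter.
- **Hypothesis** (Statistical power and analysis): "H0: TPR0 ≤ 0.80 or FPR0 ≥ 0.04". The 4% limit is justified there by the needs of general population screening.
- **Use of the controls** (Study aims): a secondary objective uses marker levels in the control group to define different positivity thresholds.

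**The concern.** In a nested case-control study meant to estimate accuracy, the controls should represent the women without the disease in the population that produced the cases. A restriction on one side only breaks that link.

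Two things are at stake. First, the FPR is judged against a limit set for general screening but measured after women with a cancer history have been removed. Any thresholds derived from the same controls inherit the restriction. Second, cancer history becomes tied to case status by design: it can occur among cases and cannot occur among controls. If an earlier cancer or its treatment changes circulating miRNA, part of a case-control difference may reflect that history and not the current breast cancer.

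The Discussion says it is unknown whether miRNA levels vary with age, other demographic parameters or smoking, and gives this as the reason for matching on age and smoking. Cancer history is instead removed from one group only.

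**Working it through.** **1. The plan's own figures.** 179 × 3 = 537 and 233 × 3 = 699, as stated. 21,000 × 0.011 = 231, against 233 stated. The article gives no formula for the 179, but one ROC-point variant, found by trying several, reproduces it:

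n = [z(0.975)√V0 + z(0.80)√V1]² / (TPR1 − TPR0)², with V = TPR(1 − TPR) + s²·FPR(1 − FPR)/3, s the slope of a binormal ROC curve (b = 1), and FPR = 0.05.

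- V0 = 0.16 + 0.1167 = 0.2767
- V1 = 0.09 + 0.0458 = 0.1358
- n = (1.960 × 0.5260 + 0.8416 × 0.3686)² / 0.01 = 179.9

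The point concerns selection, so these figures matter only for the cost of the fix.

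**2. Who can be counted, under the rules as written.**

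| Woman | Breast cancer found at screening | Not found |
|---|---|---|
| No earlier cancer | case, enters TPR | may be a control, enters FPR |
| Earlier non-breast cancer | case, enters TPR | barred, enters nothing |

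**3. Expected numbers.** The article gives no prevalence of earlier cancer. Assume a share h of 3–8%, equal in cases and non-cases.

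- Cases: 233 × 0.03 = 7 to 233 × 0.08 = 19.
- Controls under the stated rule: 0 of 699.
- Controls if the exclusion were dropped: 699 × 0.03 = 21 to 699 × 0.08 = 56.

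**4. Effect on the FPR.** Let F be the FPR in the restricted controls and f the positivity in women with an earlier cancer but no breast cancer. The FPR in the screened population is (1 − h)F + hf, so the gap is h(f − F). With F = 0.04 and f assumed:

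| h | f | Population FPR | Gap |
|---|---|---|---|
| 0.03 | 0.08 | 0.0412 | 0.0012 |
| 0.05 | 0.12 | 0.0440 | 0.0040 |
| 0.08 | 0.20 | 0.0528 | 0.0128 |

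A wider set of assumptions (h from 1% to 5%, f from 8% to 50%) gives 0.0404 to 0.063. If an earlier cancer instead makes positivity less likely, the gap reverses. At the extreme, f = 0, the restricted controls overstate the FPR by 0.03 × 0.04 = 0.0012 to 0.08 × 0.04 = 0.0032.

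**5. Could it change the FPR conclusion?** An observed 4% does not reject the null. With 699 controls the standard error at 4% is √(0.04 × 0.96/699) = 0.0074. A one-sided 5% rejection therefore needs an observed FPR of about 0.04 − 1.645 × 0.0074 = 0.0278. With F = 0.0278 in the same formula:

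- h = 0.03, f = 0.08: 0.029
- h = 0.05, f = 0.12: 0.032
- h = 0.08, f = 0.20: 0.042

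Only the most extreme corner passes 4%, and only just.

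**6. Room for lost cases.** If as many as 10% of cases were removed (233 × 0.10 = 23), about 210 would remain. The requirement is missed only after 233 − 179 = 54 cases (23%) are lost.

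**The case against.** The strongest reply is that this is a condensed article. Eligibility takes one sentence, the flow figure is not shown, and the full protocol may exclude women with earlier cancer at entry. The control criterion might then only restate a cohort condition or describe a non-case. That is possible. But the one-sided rule is itself in the text, in two places, and its ordinary meaning covers past cancers of any site. The objection is to that stated rule, not to an omission.

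Three stronger readings are tempting, and the documents do not support them.

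- **Both TPR and FPR are biased in the marker's favour.** Nothing shows that an earlier cancer pushes these miRNAs towards positivity; the analysis section allows for levels higher or lower in cases. And if the target is the general screening population, women with an earlier non-breast cancer belong among the cases, so their presence is not in itself an error in the TPR.
- **Recurrences of treated breast cancer enter the aim 1 outcome.** Follow-up is "to observe the onset of new BC cases". No passage says that a recurrence or second primary counts, and invitation lists or the full protocol may exclude such women. This would rest on silence alone.
- **The article contradicts its claim of uniformity.** The phrase "ensuring that case patients and control subjects are collected in exactly the same way" concerns how specimens are taken from a single cohort. It is not a statement about diagnostic eligibility, so the control rule does not contradict it.

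It is also fair to say that the gaps in the low and middle scenarios (0.0012 and 0.0040) are smaller than one standard error of the FPR (0.0074).

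**Conclusion.** The concern holds in a limited form. The exclusion for cancer history is stated for controls and for no one else. Followed as written, it gives an FPR for a cleaner group than the one for which the 4% limit is meant, and it leaves cancer history as a possible confounder of the case-control comparison.

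The direction is unknown and the size probably modest. The gap of about 0.1–1.3 percentage points rests wholly on assumed values for prevalence (3–8%) and positivity (8–20%). Under those values a rejection of the FPR null would be misleading only at the extreme corner. The sample size is not affected. It is still worth correcting: the limit is only 4%, random error shrinks with more controls while this gap does not, and the correction is cheap while the samples are still in storage.

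**What to change.** Before the assays are run, state one cancer-history rule that covers cases and controls alike.

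- **Other cancers (preferred):** drop the control-only exclusion, so that controls represent screening attenders without breast cancer in the same way as cases represent those with it. Add a sensitivity analysis that excludes women with any earlier cancer from both groups.
- **Previous breast cancer:** if such women are in the cohort, exclude them from both cases and controls.
- **Wording:** make the control criteria in the Statistical power and analysis section and in the Discussion agree, including on premalignant disease.
- **Source of the history:** take it from the same source for both groups. The items listed for the short questionnaire ("reproductive and BC family history, previous breast biopsies, basic physical activity level, body mass index and alcohol consumption") do not include personal cancer history. The long questionnaire covers general state of health and may supply it.

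The cost is a change of wording and one extra analysis. Dropping the exclusion for other cancers loses no one; excluding previous breast cancer may lose a few cases. Even a 10% loss leaves about 210 cases and 210 × 3 = 630 controls, above the 179 and 537 required.

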### Biomarkers analysis

The Andromeda study includes molecular analyses to evaluate circulating miRNAs and SNPs that will be performed blindly on an appropriate case-control sample extracted from the cohort of enrolled women, as soon as a minimum number of BC cases will be reached. Blinding allows avoiding that knowledge of subject’s outcome status affect the interpretation of an assay result or the care with which the specimen is handled. The prospective specimen collection plus retrospective blinded-evaluation (PRoBE) design assumed here has been proposed by Pepe et al. [29] as a good practice to follow for the pivotal evaluation of biomarker accuracy.

The selected miRNAs come from two consolidated studies [20, 21], and are suited to the screening nature of the Andromeda study.

In more detail the biomarkers to be analyzed are the following:Circulating total RNA extraction from plasma samples will be carried out with miRNeasy serum/plasma minikit (Qiagen) with minor modifications of the Exiqon protocol, implying use of a RNA carrier (batteriofage MS2 RNA, Roche Diagnostics®) to promote RNA precipitation. Cel-miR-139 will be used as spike-in control to check extraction yield and to normalize data. RNA samples will be purified on membranes and eluted with nuclease free water and stored at −80 °C. We will carefully evaluate the presence of haemolysis in our analysis and exploit our huge sample cohort to validate previous results on an independent dataset.RT-qPCR analysis of selected markers (genes, microRNAs, lncRNAs)Total RNA samples will be reverse-transcribed and amplified with specific assays for cel-miR-39, hsa-miR-1228, hsa-miR-145, hsa-miR-451, hsa-miR-222, hsa-miR-18a, hsa-miR-181a and analyzed on a qPCR apparatus with specific dedicated software. Every RNA samples will be analyzed in triplicate. Normalization of expression data will be carried out using hsa-miR-1228 [30] and cel-miR-39 as normalizers. As for SNPs also for miRNAs research findings are continuously updated, so they will be selected considering the most recent findings at the time of their extraction [31].SNP genotypingGenomic DNA will be extracted from buffy coat with High Pure PCR Template preparation kit (Roche Diagnostics®). 77 SNPs described in Mavaddat et al. [18] will be evaluated using the Personal Genome Machine (Ion Torrent) NGS apparatus.

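### Five candidate miRNAs are each evaluated singly, but alpha, power and the 179 cases are set for one test, with no primary marker, panel score or split of alpha

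*Protocol article*

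**What the plan says.** All references are to the protocol article.

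- **Study aims.** The second main aim concerns several selected miRNAs. It asks whether they are altered in cases and also whether they meet pre-set true- and false-positive rates.
- **Biomarkers analysis.** The RT-qPCR step uses "specific assays for cel-miR-39, hsa-miR-1228, hsa-miR-145, hsa-miR-451, hsa-miR-222, hsa-miR-18a, hsa-miR-181a". Of these, cel-miR-39 and miR-1228 are the normalizers, so the candidates are miR-145, -451, -222, -18a and -181a. The list can still be updated: "so they will be selected considering the most recent findings at the time of their extraction".
- **Statistical power and analysis, hypothesis.** There is one null: "H0: TPR0 ≤ 0.80 or FPR0 ≥ 0.04". The design alternative is "TPR1 = 0.90 and FPR1 = 0.05".
- **Statistical power and analysis, size.** At alpha 5% and 80% power, 179 cases and 537 controls are required. The 233 cases expected are said to exceed this, and 699 matched controls are planned.
- **Statistical power and analysis, methods.** "The discrimination ability of single biomarkers will be evaluated by means of the ROC curves". Logistic regression tests whether levels are higher or lower in cases. Three of the five miRNAs are also assessed in about 1,800 women with an affected first-degree relative, of whom about 40 are expected to join the case group.
- **Discussion.** Stored samples would allow later discovery "of novel circulating molecules whenever those selected will not satisfy our expectance".

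**The concern.** The number of markers and the number of tests in the sample-size statement do not match. The evaluation is called pivotal and has a formal null, but that null names no marker, and five markers are taken one at a time. Two readings are possible, and each leaves something in the text that does not hold:

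- Each marker is tested at the full 5%. Then 5% is not the error rate of the conclusion that some circulating miRNA is altered in breast cancer.
- Alpha is divided among the markers. Then the comparison of 233 expected cases with 179 required overstates the power, because 179 contains no allowance for the division.

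Only a single pre-named marker, or one score combining them, would make both the 5% and the 179 correct as printed. The article describes neither. At stake is whether one marker out of five that passes by chance would be reported as a pivotal result.

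**Working it through.** **Inputs from the article.** Alpha 5% (sidedness not stated), power 80%, TPR 0.80 against 0.90, null FPR 0.04, design FPR 0.05, three controls per case, 179 cases required, 233 expected, 7 − 2 = 5 candidate miRNAs.

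**Assumptions.** The correlation between marker test statistics is taken from 0 to 0.8. The ROC slope r at the working FPR f comes from an equal-variance binormal curve.

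**1. The printed size.** Let V = TPR(1 − TPR) + r²f(1 − f)/3, with V0 at TPR 0.80 and V1 at TPR 0.90. Then n = (z_α√V0 + z_β√V1)² / (0.90 − 0.80)².

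At f = 0.05: r0 = 2.715 gives V0 = 0.2767, and r1 = 1.702 gives V1 = 0.1358.

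- Two-sided 5%: (1.960 × 0.5260 + 0.8416 × 0.3686)² / 0.01 = 179.9 cases.
- One-sided 5%: 138.2 cases.

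At f = 0.04, a simpler form uses r = 3.25 (the slope at TPR 0.80) and variance 0.09 + r²f(1 − f)/3 = 0.2251. Two-sided, it gives (1.960 + 0.842)² × 0.2251 / 0.01 = 177 cases.

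So 179 fits one test at an undivided 5%. It is not uniquely reproducible, because the article gives no slope and other slopes also come close.

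**2. Chance of at least one false positive in five tests at 5%, no marker associated.** If independent: 1 − 0.95⁵ = 22.6%. With equal correlation ρ (simulated normal statistics):

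| ρ | one-sided | two-sided |
|---|---|---|
| 0.3 | 19.3% | 20.9% |
| 0.5 | 16.6% | 18.2% |
| 0.7 | 13.5% | 14.8% |
| 0.8 | 11.7% | 12.8% |

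This applies directly to the logistic tests, where a difference in either direction counts. The range is about 12–23%.

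**3. The TPR/FPR null.** The same figures apply here only if all five markers sit exactly at TPR 0.80 with FPR 0.04. If 5% is two-sided and only the favourable 2.5% tail counts, five independent tests give 1 − 0.975⁵ = 11.9%.

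Below the boundary the chance collapses. Take 233 cases, 699 controls, one-sided 5%, f = 0.04 and true TPR 0.75. The slope is 3.69, V = 0.1875 + 0.1741 = 0.3616, and the standard error is √(0.3616/233) = 0.0394. One marker passes with probability P(Z > 1.645 + 0.05/0.0394) = P(Z > 2.91) ≈ 0.0018, so any of five passes with probability about 0.9%. At true TPR 0.70 it is about 0.02%.

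**4. Effect of dividing alpha by five (first Holm step).** Scaling the printed 179:

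- Two-sided: 179 × (2.576 + 0.842)² / (1.960 + 0.842)² ≈ 267 cases.
- One-sided: 179 × (2.326 + 0.842)² / (1.645 + 0.842)² ≈ 291 cases.

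Both exceed 233. Power per marker with 233 cases:

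| Basis | Unadjusted, two-/one-sided | Alpha/5, two-/one-sided |
|---|---|---|
| Scaled from 179 | 89% / 88% | 73% / 70% |
| Step 1 formula with V0 and V1, f = 0.05 | 91% / 96% | 68% / 79% |
| Same, f = 0.04 | 89% / 95% | 63% / 76% |

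The first row is Φ(3.196 − 2.576) two-sided and Φ(2.837 − 2.326) one-sided, where 3.196 = (1.960 + 0.842)√(233/179) and 2.837 = (1.645 + 0.842)√(233/179).

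**5. A conflict to settle first.** The design value FPR1 = 0.05 lies inside the stated null (FPR of 0.04 or more). As written, the design alternative is part of the hypothesis to be rejected. This is why step 4 is shown at both values.

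**The case against.** The strongest reply is that a condensed article commonly leaves the primary marker or a multiplicity rule to the full protocol or analysis plan, which are not shown. The article also never says that one passing marker counts as success. This stands in part: the missing rule is not itself an error. It does not rescue the size statement, because a rule that divides alpha would contradict the claim that 233 cases are more than enough, and a single-marker or panel rule is not what the article describes.

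Three stronger readings are tempting, and the text does not support them:

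- **That there is a 17–23% chance of falsely validating a screening marker.** Success on the second aim needs altered levels and also the TPR/FPR criterion. For that criterion the figure is a worst case at the boundary (step 3), and requiring both conditions cannot raise it.
- **That the fallback to new molecules and the open list add further attempts.** The Discussion describes future discovery, not a repeat of the pivotal test. Updates to the list follow published findings at the time of extraction, and the assays are run blind to outcome, so they are not driven by this study's results. Neither enters the error rate.
- **That the family-history analysis adds three formal tests.** The article says only that levels will be assessed there, so an eight-test figure has no basis in the text.

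It is also fair that the adjusted power depends on an unstated slope and sidedness. For that reason a range is given.

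**Conclusion.** The point holds in a limited form. The article fixes a size for one test at an undivided 5% and plans single-marker evaluation of five miRNAs with no designated primary. For the tests of altered levels, the chance of at least one false positive when no marker is associated is up to about 23%. The lower end of about 12% assumes a correlation of 0.8, and the article gives no correlation. For the TPR/FPR null, excess error is confined to markers at or very near the boundary; if all five had TPR 0.75 at FPR 0.04, the chance that any passes would be about 1%. If alpha is divided instead, all the calculations in step 4 with 233 cases fall below the stated 80%. This calls for a change of wording and, under one option, a restated power. It does not undermine the specimen collection or the blinded design.

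**What to change.** Before case status is linked to the assay results, fix the marker list and adopt one of these in Biomarkers analysis and in Statistical power and analysis:

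- **(a)** Name one primary miRNA, or one panel score with its combination rule specified in advance, for the TPR/FPR test at 5%. The other miRNAs become secondary. The printed 179 is unaffected by this choice.
- **(b)** Keep all five as equals and apply Holm control at 5% overall, to the TPR/FPR tests and to the logistic tests, and restate the power.

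Under either option:

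- State whether alpha is one- or two-sided, and the ROC slope assumed.
- Reconcile FPR1 = 0.05 with the null of FPR 0.04 or more before any power is restated.
- Label the family-history results exploratory.
- State that a molecule discovered in these cases and controls will not be presented as validated in them.

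**Cost.** Wording only, with no new samples or assays. Option (a) costs no power but commits to one marker or score. Option (b) lowers power per marker at the first Holm step to roughly 63–79% with 233 cases; restoring 80% by scaling the printed figure would need about 267 (two-sided) or 291 (one-sided) cases.
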